## Abstract

**Background:**

People with hereditary spastic paraplegia (HSP) experience difficulties adapting their gait to meet environmental demands, a skill required for safe and independent ambulation. Gait adaptability training is possible on the C-Mill, a treadmill equipped with augmented reality, enabling visual projections to serve as stepping targets or obstacles. It is unknown whether gait adaptability can be trained in people with HSP.

**Aim:**

The aim of Move-HSP is to study the effects of ten 1-h sessions of C-Mill training, compared with usual care, on gait adaptability in people with pure HSP. In addition, this study aims to identify key determinants of C-Mill training efficacy in people with pure HSP.

**Method:**

Move-HSP is a 5-week, two-armed, open-label randomized controlled trial with a cross-over design for the control group. Thirty-six participants with pure HSP will be included. After signing informed consent, participants are randomized (1:1) to intervention or control group. All participants register (near) falls for 15 weeks, followed by the first assessment (week 16), and, thereafter, wear an Activ8 activity monitor for 7 days (week 16). The intervention group receives 10 sessions of C-Mill training (twice per week, 1-h sessions; weeks 17–21), whereas control group continues with usual care (weeks 17–21). Afterwards, both groups are re-assessed (week 22). Subsequently, the intervention group enter follow-up, whereas control group receives 10 sessions of C-Mill training (weeks 23–27), is re-assessed (week 28), and enters follow-up. During follow-up, both groups wear Activ8 activity monitors for 7 days (intervention group: week 23, control group: week 29) and register (near) falls for 15 weeks (intervention group: weeks 23–37, control group: weeks 29–43), before the final assessment (intervention group: week 38, control group: week 44). The primary outcome is the obstacle subtask of the Emory Functional Ambulation Profile. Secondary outcomes consist of clinical tests assessing balance and walking capacity, physical activity, and fall monitoring.

**Discussion:**

Move-HSP will be the first RCT to assess the effects of C-Mill gait adaptability training in people with pure HSP. It will provide proof of concept for the efficacy of gait adaptability training in people with pure HSP.

**Trial registration:**

Clinicaltrials.gov NCT04180098. Registered on November 27, 2019.

**Supplementary information:**

**Supplementary information** accompanies this paper at 10.1186/s13063-020-04932-9.

## Background

Hereditary spastic paraplegia (HSP) is a heterogeneous group of neurodegenerative disorders, caused by retrograde axonal degeneration of the corticospinal tracts, fasciculus gracilis fibers, and to a lesser extent, the spinocerebellar fibers [1–3]. Pure forms of HSP are clinically characterized by progressive spasticity, muscle weakness, and reduced proprioception in the lower extremities, as well as difficulties in making rapid (alternating) leg movements [4–6]. Additional symptoms are present in complex forms of HSP, including mental retardation, epilepsy, ataxia, peripheral neuropathy, or optic atrophy [1, 4, 7]. For people with pure HSP, gait and balance impairments are among the most disabling symptoms. They especially experience difficulties when forced to adapt their gait to meet environmental demands, hampering the ability to walk safely and independently in the community [4, 8–11]. A recent study reported that 57% of pure HSP patients fell at least twice a year, and 73% experience fear of falling [11]. Incorporating gait adaptability training in rehabilitation programs for people with pure HSP seems, therefore, logical and potentially beneficial [4, 11, 12].

A limited number of task-specific gait interventions have shown to improve walking capacity in people with pure HSP. Twenty-five sessions of robot-assisted exoskeleton and overground walking improved walking velocity and balance capacity [13]. In addition, eighteen sessions of robotic Lokomat training increased walking speed, balance capacity, and quality of life [9]. Even though these results are promising, the interventions lacked tasks that promote gait adaptability. As a consequence, it remains unknown whether people with pure HSP will benefit from gait adaptability training [4]. Furthermore, it is unclear how to tailor gait rehabilitation programs to the individual patient with HSP as it is currently unknown which determinants can predict training efficacy.

To fill this gap, Move-HSP is the first randomized controlled trial to provide proof of concept for the efficacy of gait adaptability training in people with pure HSP. The training takes place in a safe environment on the C-Mill, a treadmill providing augmented reality via visual projections onto the treadmill. Participants will train obstacle negotiation, precision stepping, and unexpected accelerations and decelerations. Its feasibility and efficacy have been described in multiple neurological populations, including patients with stroke [14], cerebellar ataxia [15], and multiple sclerosis [16]. Currently, the clinical experience with gait adaptability C-Mill training for people with pure HSP is positive, but the scientific evidence is lacking [4].

### Objectives

This study aims to provide an essential step towards evidence-based and individually tailored gait rehabilitation in people with HSP. The objectives are twofold:
To study the effect of ten 1-h sessions of C-Mill training on gait adaptability in people with pure HSP.To identify key determinants of C-Mill training efficacy in people with pure HSP.

## Methods/design

### Regulation statement

Move-HSP will be conducted according to the principles of the Declaration of Helsinki (64th WMA General Assembly, Fortaleza, Brazil, October 2013) and the Medical Research Involving Human Subjects Act. The protocol is written in accordance with the SPIRIT 2013 checklist.

### Study design and setting

Move-HSP is a 5-week, single-center, two-armed, open-label, randomized controlled trial (RCT), with a cross-over design for the control group, as they receive the intervention after a waiting list period. The study is conducted at the Radboud University Medical Center (Radboudumc) within the Center of Expertise for Parkinson & Movement Disorders; Nijmegen, The Netherlands. C-Mill training can be given at the Radboudumc (Nijmegen, The Netherlands), Paramedisch centrum Rembrandt (Veenendaal, The Netherlands), Stichting Tante Louise (Bergen op Zoom, The Netherlands), and Fysiotherapie De Lindehoeve (Voorschoten, The Netherlands). Other training locations may be added while the study is ongoing, depending on the success of participant inclusion.

### Recruitment and selection

Participants will be recruited at the Center of Expertise for Parkinson & Movement Disorders of the Radboudumc (part of the European Reference Network for Rare Neurological Diseases (ERN-RND)). The treating physician informs the patient about Move-HSP and asks for permission whether the investigator (LV) may contact the patient. In addition, a request to participate will be sent to members of the HSP patient organization “Spierziekten Nederland”. Those who are interested can contact the investigator and will receive an information letter. After 2 weeks, the investigator (LV) will contact those who expressed their interest and ask for their final decision. If patients agree to participate, eligibility is checked. After inclusion, participants can leave the study at any time without consequences.

### Eligibility

For inclusion, participants will have to meet the following inclusion criteria:
Diagnosis of pure HSP by a neurologist specialized in inherited movement disorders. Diagnosis is based on inheritance pattern and clinical examination, and when available, molecular diagnosis.Age between 18 and 70 years oldAbility to walk barefoot on a level ground for 50 m without a walking aid (use of orthotic devices or orthopedic shoes is allowed)

Participants will be excluded if they suffer from other neurological, orthopedic, or psychiatric conditions, or if patients underwent an HSP-related surgical procedure of the lower extremities.

### Group allocation and blinding

Participants will be allocated at random to the intervention group or to the (waiting list) control group following a 1:1 ratio. Randomization will be stratified based on disease duration (2 categories: 0–15 years; > 15 years) in blocks with a variable size (*n* = 4 or *n* = 6) to prevent an uneven distribution between groups. To determine disease duration, participants are asked for the year of symptom onset. Randomization will be performed in CastorEDC, a web-based data management system for academic studies (www.castoredc.com). Blinding of participants is not possible, as participants will know whether they receive C-Mill training or continue with usual care. The primary investigator (LV) takes part in the training sessions as a physical therapist and, therefore, cannot be blinded either.

### Participant timeline

The outline of this study is shown in Fig. 1. Following inclusion, participants are randomly allocated to either the intervention group or the control group (waiting list). During the first 15 weeks, all participants register (near) falls in a digital fall calendar. Thereafter, participants will have the first assessment at the movement laboratory (Radboudumc; week 16). Following this assessment, participants wear an Activ8 activity monitor for seven consecutive days (week 16). Thereafter, the *control group* enters a waiting period of 5 weeks (weeks 17–21), whereas the *intervention group* starts with 5 weeks of gait adaptability training on the C-Mill (weeks 17–21). Each session lasts 1 h and takes place twice per week. Subsequently, both groups are re-assessed (week 22). Following this second assessment, the intervention group enters the follow-up period, whereas the control group wears the Activ8 activity monitors for 7 days (week 22), starts 5 weeks of gait adaptability training (weeks 23–27), has the third assessment (week 28), and thereafter, enters the follow-up period. During follow-up, both groups wear Activ8 activity monitors during the first week (intervention group: week 23, control group: week 29) and, additionally, register (near) falls for 15 weeks (intervention group: weeks 23–37, control group: weeks 29–43). After follow-up, participants have a final assessment in the movement laboratory (intervention group: week 38, control group: week 44).

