### Procedure and assessments

All outcome measurements will be collected during the assessments at the movement laboratory (Table 1). The intervention group is evaluated three times: pre C-Mill training (week 16), post C-Mill training (week 22), and at the end of the follow-up (week 38). The control group is evaluated four times: pre waiting-list (week 16), post waiting-list (week 22), post C-Mill training (week 28), and at the end of the follow-up (week 44). The assessments will follow a standardized protocol and are conducted by the primary investigator (LV) who is trained to perform the outcome measurements. As the primary investigator takes part in the training sessions, outcome assessment cannot be blinded. During all assessments, the use of orthotic devices and/or orthopedic footwear is allowed depending on the task. No other (walking) aids are allowed. If participants use any orthotic or orthopedic device during a task, this will be registered and kept constant throughout the consecutive assessments.

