### Primary outcome

The primary outcome is gait adaptability as measured with the obstacle subtask of the Emory Functional Ambulation Profile (E-FAP). Participants are asked to negotiate a 10-m course in which two wooden blocks (100(l) × 10(w) × 5(h) cm) and a bin are placed along the walkway. The instruction given is to complete the task as fast as possible but keep your own safety in mind. The number of seconds needed to complete the task is registered. A faster time score indicates better gait adaptability. The obstacle subtask of the E-FAP has previously been used as an outcome measure for gait adaptability in several neurological populations [14, 15]. The full protocol is available online and via Wolf et al. [25].

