### Trial status

Participant recruitment has started in November 2019 and is currently ongoing. So far, no assessments in the movement laboratory have yet been conducted. It was originally anticipated that a total of 10 months would be needed to complete the recruitment and 24 months to complete the entire protocol, but the current SARS-CoV-2 pandemic will undoubtedly lengthen these periods to an unforeseeable extent. This study protocol is based on protocol version 5, dated October 31, 2019. An amendment to add training locations was approved on February 18, 2020.

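### Randomisation takes place 15 weeks before the week-16 baseline in an open-label trial, so the E-FAP covariate can be measured with the arm known, and early leavers count as randomised losses without data

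*Protocol article*

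**What the plan says.** The order of events is given twice. The abstract (Method) states: "After signing informed consent, participants are randomized (1:1) to intervention or control group". Participant timeline agrees: "Following inclusion, participants are randomly allocated to either the intervention group or the control group (waiting list"), then "During the first 15 weeks, all participants register (near) falls in a digital fall calendar", then "Thereafter, participants will have the first assessment at the movement laboratory (Radboudumc; week 16"). Seven days of activity monitoring follow in week 16. Training or waiting occupies weeks 17–21, and both arms are re-assessed in week 22.

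On blinding, Group allocation and blinding says: "Blinding of participants is not possible, as participants will know whether they receive C-Mill training or continue with usual care". Procedure and assessments has one investigator, who also helps deliver the training, carry out the assessments: "As the primary investigator takes part in the training sessions, outcome assessment cannot be blinded".

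The primary outcome is the time taken on an obstacle course. Under Primary outcome: "The instruction given is to complete the task as fast as possible but keep your own safety in mind". Statistical analysis specifies an ANCOVA of the post-intervention value on the pre-intervention value, with group as the factor. Sample size goes from 32 to 36 participants for 10% attrition. Trial status reports that recruitment began in November 2019 and adds: "So far, no assessments in the movement laboratory have yet been conducted".

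**The concern.** An ANCOVA covariate should be a quantity that allocation cannot influence. When baseline is measured before randomisation, the design guarantees this. Here 15 weeks separate allocation from baseline, and the test depends on how hard and how cautiously the participant walks. It is timed by someone who can know the arm. Any effect of that knowledge on the week-16 time enters the adjusted treatment estimate, and no later analysis can separate it out.

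Two further features add to the exposure. The request to keep therapy constant (Control group) covers only the five waiting weeks, so behaviour in weeks 1–15 is not controlled. And a participant who leaves in those weeks contributes neither the covariate nor the primary outcome, yet belongs to the randomised population. If such losses differ between arms, no adjustment for baseline E-FAP is possible.

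The article gives no reason for allocating so early. Procedures are identical in both arms until week 17, and stratification needs only the year of symptom onset, which is known at inclusion and does not change.

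**Working it through.** **Inputs from the protocol article.** Randomisation at inclusion; baseline in week 16; primary assessment in week 22; final assessment in week 38 (intervention) or week 44 (control) (Participant timeline). Target difference 1.75 s, 32 evaluable participants, 10% attrition, 36 included (Sample size). How the 32 was derived does not bear on this point.

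**Inputs assumed.** The article gives no expectation effect, no pre-post slope and no timing of attrition. The values below show sensitivity only.

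**1. The plan's attrition figure.** 32 / (1 − 0.10) = 35.6, rounded up to 36, as stated. Expected losses: 36 × 0.10 = 3.6.

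**2. Losses before baseline, if spread evenly over the period shown.**
- To week 22: 3.6 × 15/22 = 2.5
- To week 38: 3.6 × 15/38 = 1.4
- To week 44: 3.6 × 15/44 = 1.2

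So about 1.2 to 2.5 of the 3.6 expected losses would be randomised participants with no laboratory data.

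**3. Bias in the ANCOVA estimate.** Let b0 and b1 be the between-arm shifts (in seconds) that knowledge of the arm causes at week 16 and week 22.

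Bias = b1 − slope × b0

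Absolute bias for b0 = 0.5 s, with its share of the 1.75 s target:

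| Assumed slope | Baseline only (b1 = 0) | Shift persists (b1 = 0.5) |
|---|---|---|
| 0.5 | 0.25 s (14%) | 0.25 s (14%) |
| 0.7 | 0.35 s (20%) | 0.15 s (9%) |
| 0.8 | 0.40 s (23%) | 0.10 s (6%) |
| 0.9 | 0.45 s (26%) | 0.05 s (3%) |

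At slope 0.8: 0 − 0.8 × 0.5 = −0.4 s, and 0.5 − 0.8 × 0.5 = 0.1 s. The sign depends on which arm is slowed or hurried, and the article offers no basis for choosing.

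**4. What moving randomisation does to this term.** A baseline taken before allocation sets b0 = 0 and leaves bias = b1. The baseline part disappears. A week-22 shift of 0.5 s would then appear in full as 0.5 s, where a persistent shift had been partly cancelled (0.1 s at slope 0.8). The change protects the covariate; it does not deal with the unblinded outcome.

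**The case against.** The strongest reply is that the covariate is still measured before any training, so it is not a mediator of treatment, and that the bias figure depends on what is assumed for week 22. The same aware participants and unblinded assessor are present at both visits, and a persistent shift largely cancels when the slope is high. This stands: 0.4 s cannot be presented as the expected bias, and unblinded week-22 assessment is the exposure that remains after the change.

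Several stronger readings are tempting but lack support:
- **That participants are told their arm at inclusion.** No text dates disclosure, and the flowchart and schedule figures are not shown. Early knowledge is the natural reading of an open-label trial with no withholding step, but it is an inference.
- **That nothing is measured before week 16.** Falls and near falls are recorded in weeks 1–15; only laboratory and activity data are absent.
- **That the pandemic widens this interval.** Trial status says only that recruitment and completion of the protocol will take longer.
- **That people told to wait will leave more often.** Everyone waits until at least week 17, and controls start the same ten sessions in week 23, six weeks later. Differential loss is possible but not shown.
- **That the fall results are compromised.** Falls are only described, and near falls may be tested with a signed-rank test, which is a within-person comparison. No between-arm fall analysis is described.

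Early allocation may also help in booking twice-weekly sessions at several training locations. That is a practical convenience, and the article does not offer it as a reason.

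**Conclusion.** The point holds as a design weakness that is cheap to remove. Two sections put randomisation 15 weeks before baseline, and nothing in the article prevents the primary covariate from being measured with the arm known. Losses during the diary period are randomised losses with no E-FAP data: about 1.2 to 2.5 of 3.6, assuming even attrition to week 44 or to week 22 respectively.

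The bias in the primary estimate cannot be sized from the document. With an assumed 0.5 s baseline shift and slope 0.8, its absolute value is about 0.1 s if the shift persists and 0.4 s if it is confined to baseline. Neither the shift nor the slope has a source in the article. A reader might infer that the primary comparison is invalid as planned. The document does not support that: the covariate precedes training, and neither a baseline shift nor arm-specific dropout is shown. It is a worthwhile improvement, not a must-fix error.

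**What to change.** Perform the CastorEDC randomisation after the week-16 laboratory assessment and the 7-day activity recording, just before week 17, with the stratification and block sizes unchanged. Consent, the fall calendar and the week-16 tests then form a pre-randomisation run-in. At baseline neither participant nor assessor can know the arm, and those who leave during the run-in can be replaced before they are randomised.

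Participants already randomised keep their allocation and are flagged. A sensitivity analysis restricts the primary ANCOVA to those randomised after baseline. The article does not say how many have been randomised, so that subset may be small.

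If allocation is in fact already withheld until after week 16, the protocol should say so. Withholding alone would protect the covariate, but diary-period leavers would remain randomised losses.

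The cost is a short amendment, training slots booked at short notice, and a cohort randomised at two different time points. Visits, tests and sample size do not change. Because no laboratory assessment had been done at the time of writing, the change is cheapest now. It does not remove the unblinded week-22 assessment, which should still be reported as a limitation.

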**Fig. 1 Fig1:**
[figure not shown]
Flowchart of the study protocol

During Move-HSP, all participants can continue their usual care. For some participants, this may include local intramuscular injections of botulinum toxin (BTX). To limit the influence of BTX injections on the outcomes, the scheduling of the assessments will consider the date of the BTX injections. BTX injections induce an effect on muscle spasticity approximately 2 weeks post-injection. The maximum effect is reached around 6–8 weeks, after which it gradually subsides [17, 18]. Participants who receive BTX injections in the lower extremities will have the pre-intervention assessment 4 weeks post-injection, and the post-intervention assessment 10 weeks post-injection. In addition, it will be monitored whether the dosage of oral antispasmodic changes during the trial.

### Control group

The eighteen participants attributed to the control group are asked to continue with their daily routine and usual care during the 5 weeks on the waiting list. If therapy is part of the usual care, participants are requested to continue with the same frequency and composition during the waiting period.

### Intervention: C-Mill training

Gait adaptability training takes place on the C-Mill (Motek Medical, Culemborg, The Netherlands). The C-Mill is a treadmill, providing augmented reality via visual cues projected onto the treadmill. The projections are either stepping targets or obstacles that challenge the participants to adjust their steps accordingly. The training sessions take place during five consecutive weeks, twice per week during 60-min sessions. In total, participants will train gait adaptability on the C-Mill for 10 h.

The C-Mill protocol is based on clinical experience and finalized after a focus group discussion with expert physical therapists. The training sessions are logged to ensure compatibility and a consistent progression. Each session starts with a 10-min warming-up, followed by five training blocks (Fig. 2, video). Each training block lasts approximately 8 min. Block A targets precision stepping by practicing accurate foot placement on the projected stepping tiles. Block B targets obstacle negotiation by avoiding the projected obstacles. Block C elicits changes in the direction of progression by using a variety of slalom trajectories. Block D targets precision acceleration and deceleration, as the participants must walk within a projected square that moves forward and backward on the treadmill. Block E challenges walking at different walking speeds. Block F is the endgame, a 5-min track that combines several gait adaptability components in an interactive way. All sessions end with a cooling-down. To further promote the level of variability, each training block consists of small components (i.e., for block A: Stepping Tiles: belt speed will momentarily increase; width between the stepping stones will momentarily decrease). In addition, different walking speeds are used: 100% is the participant’s comfortable walking speed on the treadmill. This will be determined during the first training session. The belt speed will be manually increased until the participant experiences it as comfortable. The therapist will then increase the belt speed with 0.3 m/s and slowly decrease the belt speed until the participant again experiences it as comfortable. The average of both speeds will be used to set the comfortable walking speed. Other percentages (e.g., 40%, 70%, 120%) are derived from this reference speed. The C-Mill training will be carried out by a physiotherapist with C-Mill certification. Progression over the training period is initiated and controlled by this therapist and based on the patient’s capacity and performance. It comprises of increasing the level of task variability, increasing obstacle size, and the addition of a dual task, for example the use of the auditory Stroop task. During the Stroop task, participants listen to an audiotape presenting a random sequence of the words “high” or “low”, expressed in either a low-pitched voice or a high-pitched voice. They are asked to respond aloud indicating the pitch of the word (“high” or “low”), while ignoring the (randomly conflicting) semantic meaning of the word.
